**Gantt chart & milestone**

| **Research activities** | **2023** | **2024** | | **2025** | | **2026** | |
| --- | --- | --- | --- | --- | --- | --- | --- |
| **Jul-Dec** | **Jan-Jun** | **Jul-Dec** | **Jan-Jun** | **Jul-Dec** | **Jan-Jun** | **Jul-Dec** |
| Ethical application and approval |  |  |  |  |  |  |  |
| Data collection |  |  |  |  |  |  |  |
| Data analysis and interpretation |  |  |  |  |  |  |  |
| Thesis write-up and submission |  |  |  |  |  |  |  |

| 1. Ethical application and approval completed by December 2023 |
| --- |
| 1. Data collection completed by June 2025. |
| 1. Data analysis and interpretation completed by December 2025 |
| 1. Thesis write-up and submission completed by December 2026 |

**Budget proposal [from the Open Project of Psychiatry and Neuroscience Discipline of Second Affiliated Hospital of Xinxiang Medical University (2022-xyefykfkt-003)]:**

| **Vote**  *Vot* | **Budget Details & Justification**  *Perincian Bajet & Justifikasi* | **Amount requested by researcher (RM)**  *Amaun yang dipohon oleh penyelidik (RM)* | | |
| --- | --- | --- | --- | --- |
| **Year 1**  *Tahun 1* | **Year 2**  *Tahun 2* | **Year 3**  *Tahun 3* |
| **11000**  Salary and wages  *Gaji dan upah* |  |  |  |  |
| **21000**  Travelling expenses  and subsistence  *Perbelanjaan Perjalanan dan Sara Hidup* |  |  |  |  |
| **23000**  Communication and Utilities (Phone,Fax, Postage etc)  *Perhubungan dan Utiliti*  *(Tel,Faks,Pos, dll)* |  |  |  |  |
| **24000**  Rental  *Sewaan* |  |  |  |  |
| **27000**  Research Materials & Supplies (including Animals, Plants, Disposables, etc.)  *Bekalan & Bahan-bahan Lain (termasuk Haiwan, Pokok dan Bahan Pakai Habis)* | Stationary:  • A4 Paper (5 rims) @ RM12 per rim: RM12 x 6 rims= RM 72 | 24 | 24 |  |
| **28000**  Maintenance and Minor Repair Services  *Penyelenggaraan dan Pembaikan Kecil* |  |  |  |  |
| **29000**  Professional services & other services (printing & hospitality, honorarium, conference fee, journals page charges)  *Perkhidmatan ikhtisas dan perkhidmatan lain-lain (percetakan hospitaliti, honorarium, yuran persidangan & penerbitan)* | (1) Printing:  Photostat copy of questionnaires: at RM0.10 per page x 30 pages x 108 subjects = RM 324 per assessment x 4 assessments = RM 1296  (2) Honorarium of subjects:  RM 20 per subject x 108 subjects x 4 assessments =  RM 10,560 | 1,296  8,640 |  |  |
| **35000 (> RM1,000)**  Equipment[Please provide quotation]  *Peralatan [Sila berikan sebutharga]* |  |  |  |  |
| **TOTAL AMOUNT** | | 9,960 | 24 |  |
| **GRAND AMOUNT** | | **RM 9,984** | | |

**Ethical consideration(s) [if applicable]:**

1. **Subject vulnerability**

Some of the questions asked in the study may cause some subjects to be disturbed. All subjects developed any mental disturbances while participating in the study, they will be recommended for referrals to Henan Mental Hospital, Henan, China (nearest psychiatric service available). In addition, prior to referral, rescue medication such as benzodiazepine will be administered to calm down patients. In addition, subjects will be provided with counselling services from Henan Mental Hospital, Henan, China if needs arise during the study when they experienced mental disturbances. All subjects will be assured anonymity of personal information when they are offered to participate in the study and assured that all the benefits which they were entitled to will be provided if they decided to withdraw from the study. Finally, the subjects will be recommended for referral to support group, such as Alcoholics Anonymous once they have completed the study.

Specific risk may also occur in different groups of alcohol dependent subjects:

1. those who are unemployed may also present with financial constrain and difficulty to get a job. We may recommend for referral to social workers for financial aid and for job manager and occupational therapists in the community psychiatry team in the Department of Psychiatry, 2nd Affiliated Hospital, XXMU for assistance in seeking the right job and for job training.
2. those who have family members may place the close family members at risk of domestic violence and various psychosocial issues. Hence, we may offer help to family members for mental health screening and referrals to counsellors or Department of Psychiatry, 2nd Affiliated Hospital, XXMU for further management.
3. those who are having marital issues with spouse may be recommended for marital counselling under the Department of Psychiatry, 2nd Affiliated Hospital, XXMU.
4. those in the placebo group may be at risk of relapse and experience mental disturbances along the course of the study. Rescue medication such as benzodiazepine may be administered to relieve withdrawal symptoms and if you opt to withdraw from the study, immediate referral to Department of Psychiatry, 2nd Affiliated Hospital, XXMU for further treatment will be carried out.

Subjects may also withdraw from the study should an adverse event occurs. Adverse event (AE) is any untoward medical occurrence in a subject administered a trial intervention that does not necessarily have a causal relationship with this treatment. An AE can be any unfavorable and unintended sign, symptom, or disease temporarily associated with the use of investigational intervention, whether or not related to the investigational intervention. Subjects will be issued with a study card with the contact details of the research team and they are encouraged to maintain close contact by phone, to report any AE occurring in subjects. If the case of adverse event (AE), the event is reported in the adverse event section in the Case report form (CRF) and serious adverse event report is filled if necessary (Figure 5). The details to be reported include the name of the event, date of onset and date of recovery, severity, relationship to the study treatment, measures taken regarding study treatment, treatment of adverse event and outcome of the event (resolved/ongoing). Some reasons that may lead to subjects withdrawing from the study in cases of AE are:

● Presence of adverse reactions not related to the study, but subjects feel uncomfortable to continue this study.

● Presence of adverse reactions that may be related to the study, such as unusual illnesses which started upon this intervention.

● Unusual changes in behavior, temperament, routine, etc of subjects, which started upon this intervention.

● Any suspected or unexpected adverse events that is not consistent with the general acceptance of the ACT and MBSR administration. In general, psychotherapy should not exhibit any side effects or health detrimental effects.

`

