**Sampling method and subject recruitment (randomization and blinding)**

A single-blind randomized controlled trial design has been chosen. Randomization for the parallel prevention phase will be carried out after checking the inclusion and exclusion criteria. The eligible AD patients will be randomized 1:1:1 ratio to the three arms of the study according to a computer generated, blocked randomization list. The eligible patients will be assigned to the probiotics group, ACT group, and control group with a treatment code concealed in a closed envelope. The randomization will be performed by the study statistician, who had no contact with the patients and not involve in the research project. The statistician is trained to randomize subjects who first enrol in the study into the three groups using computer system for randomization purpose. The allocation sequence will not be available to any member of the research team until databases had been completed and locked. Data collection will be performed by research assistants who were not involved in the study and do not know the objectives of the study. While data analysis will be carried out by the statisticians not involved in the study. Hence, this study is blinded to the researchers but not blinded for the subjects as the ACT group has no parallel control group.

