***Test drug and treatment plan***

Test drug: Probiotic powder, specification: 2g:0.1g (Probionic Corp., South Korea.).

Placebo drug: Maltodextrin, Specification: 2g:0g (Probionic Corp., South Korea.).

The probiotics, placebo and medications for conventional treatment will be provided by the 2nd Affiliated Hospital of XXMU. There are no other sponsors. The test drug contained both probiotics and prebiotics, and both the test drug and the placebo drug were light yellow powder with no difference in taste. The probiotic powder used in the test drug was maltodextrin as the carrier, which was the same as the placebo drug. Both investigational and placebo drugs should be kept in the temperature range of less than 30 ° C as recommended by the manufacturer.

Treatment: In addition to conventional drug therapy for alcohol dependence, the following interventions were applied to each group:

Routine treatment: alcohol detoxification treatment was carried out at the early stage of admission, mainly with benzodiazepine replacement therapy, while adequate supplementation of B vitamins, strengthening symptomatic supportive treatment, and corresponding antipsychotic drugs, antidepressants or emotional stabilizers were given according to the condition. Benzodiazepines are gradually discontinued after withdrawal symptoms disappear (2 weeks).

Probiotics + conventional drug therapy group: on the basis of conventional drug therapy, probiotics powder 2g, mixed into water or milk, dissolved and oral.

Placebo + conventional drug treatment group: on the basis of conventional drug treatment, maltodextrin of the same weight as the test drug treatment group was mixed into water or milk and orally dissolved.

Frequency of probiotics and placebo treatment: once a day, each time 2g, 8 weeks.

ACT treatment group: Enrolled AD patients will be treated under the ACT protocol for eight weeks. Once a week, each treatment lasted about 1 hour.

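### Benzodiazepine rescue is described twice without reconciliation, and the statement on withdrawal symptoms is tied to the placebo group, which the research team is not allowed to identify

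*Protocol*

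**What the plan says.** Both statements are in the protocol's Ethical consideration(s), under Subject vulnerability.

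- The opening paragraph is general: "All subjects developed any mental disturbances while participating in the study, they will be recommended for referrals to Henan Mental Hospital". It continues that "prior to referral, rescue medication such as benzodiazepine will be administered to calm down patients".
- A list of specific risks in different groups follows. Its fourth item begins "those in the placebo group may be at risk of relapse and experience mental disturbances along the course of the study" and goes on: "Rescue medication such as benzodiazepine may be administered to relieve withdrawal symptoms".

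Three other places bear on this:

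- The section on sampling, randomization and blinding states: "The allocation sequence will not be available to any member of the research team until databases had been completed and locked".
- The test drug and treatment plan makes the probiotic and placebo powders alike in colour and taste. It gives all arms benzodiazepines for the initial detoxification, tapered once withdrawal symptoms have gone, which it puts at 2 weeks.
- The Data analysis section names CIWA-Ar, the withdrawal scale, as one of four primary outcome scores.

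**The concern.** Investigators need to know from the text who may receive rescue, for what, and whether it is expected or optional. The two statements answer these questions differently, and one answer depends on knowing the arm. Two things are at stake. The first is the blind: probiotic and placebo patients cannot be told apart without the code. The second is comparability. A rescue drug that is offered by arm becomes a co-intervention that differs between arms, and the rescue in item 4 is aimed at what CIWA-Ar measures.

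**Working it through.** **Step 1. The two statements side by side.**

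| Element | Opening paragraph | Item 4 |
| --- | --- | --- |
| Who | all subjects | placebo group |
| Event named | mental disturbance | relapse and mental disturbance |
| Purpose of the drug | to calm, before referral | to treat withdrawal symptoms |
| Force | *will* be given | *may* be given |
| Referral | Henan Mental Hospital | Department of Psychiatry, 2nd Affiliated Hospital, for those who leave the study |

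A mental disturbance in a placebo patient falls under both columns. For that patient the force and the stated purpose differ. The referral site differs too, although item 4 links its site to leaving the study.

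**Step 2. Is rescue for withdrawal symptoms extended to the other arms elsewhere?** The treatment plan gives benzodiazepines to every arm, but for detoxification early in the admission, with a taper at about 2 weeks. The opening ethics paragraph reaches every arm, but its trigger is mental disturbance. For withdrawal symptoms after a later relapse, item 4 is the only text, and it names one arm.

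**Step 3. Can a provision tied to the placebo group be applied?** The allocation sequence is withheld from the whole research team until lock, and the powders are matched. ACT patients can be recognised from their weekly sessions, so the difficulty falls on probiotic versus placebo. There the team cannot act on the arm without the code.

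**Step 4. Direction and size of any effect on CIWA-Ar.** Let D be the difference in mean score (placebo minus active) without rescue. Let p and a be the shares of placebo and active patients whose rescue still acts on the score at the visit. Let b be the mean fall in score from rescue, taken as the same in both arms. Then:

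observed difference = (placebo mean − b × p) − (active mean − b × a) = D − b × (p − a)

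- Equal use (p = a): the difference stays at D, with no narrowing.
- Use differing by 0.10, 0.30 or 0.50 (assumed): narrowing of 0.1b, 0.3b or 0.5b.

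The documents give no value for D on CIWA-Ar, nor for b, p or a. The sample size section uses OCDS and HAMD, and neither is a primary outcome of this trial. The direction therefore follows if placebo patients receive more rescue. The size cannot be calculated.

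**The case against.** The strongest reply is that item 4 is a note on risk and not an exclusive rule. Its list is introduced as additional to the general paragraph and sits beside unemployment, family and marital problems. It speaks to the subject directly ("Rescue medication such as benzodiazepine may be administered to relieve withdrawal symptoms and if you opt to withdraw from the study"). Nothing says *only*, and nothing denies rescue to another arm. Different purposes may explain the different force. Treatment prompted by symptoms can be given to anyone without the code. This reply stands against a reading that a reader might infer, that probiotic and ACT patients are barred from rescue and that the blind must be broken. It does not remove the ambiguity: withdrawal rescue after detoxification is still written down for one arm alone.

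A reader might also infer that the contrasts *would* shrink, on craving as well as withdrawal, with a calculable loss of power. The documents do not support this:

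- The Problem statement calls the effect of drug therapy on craving very limited, and no benzodiazepine effect on craving is given.
- The Operational definition section has withdrawal improving by seven days, while the post-intervention scores are taken at 8, 12 and 24 weeks. An effect on CIWA-Ar at those visits needs a relapse, with rescue close to the visit.
- Rescue open to all arms dilutes the contrast only if its use differs by arm. That is true of need-driven rescue in general and is no error here.

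Finally, the handling of rescue in the analysis may be in a statistical analysis plan that is not shown, so its absence from the protocol's Data analysis section is not a fault. The CRF already has an adverse event section with onset and recovery dates and the treatment of the event. That would capture some rescues, but only those reported as adverse events, and the dates listed are those of the event.

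The protocol also says that "this study is blinded to the researchers but not blinded for the subjects as the ACT group has no parallel control group", while its Research design section says double-blind. Whichever label is meant, the researchers are to be blind, so the conflict with item 4 remains.

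**Conclusion.** The point holds as a contradiction to be reconciled. The protocol has two benzodiazepine rescue statements that differ in coverage, purpose and force, and the one on withdrawal symptoms refers to an arm that the team may not know before database lock. This rests on the text alone and needs no assumed figure.

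The statistical consequence is conditional. If item 4 is applied by arm, it needs unblinding and could narrow the probiotic-placebo and ACT-placebo contrasts on CIWA-Ar. That requires more rescue in placebo than in the other arms and an effect still present at the visit. The narrowing is b × (p − a), nil when use is equal, and otherwise of unknown size. No claim is made about craving scores or power.

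**What to change.** - Reconcile the two statements, with each other and with the section on randomization and blinding, into one statement that does not refer to the allocated arm. Who is treated, for what and how is for the investigators to decide.
- Record the date and amount of each rescue on the CRF, whether or not the episode is reported as an adverse event.
- Report rescue use by arm, so that readers can see whether it differed and how close to the CIWA-Ar visits it fell.

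The cost is a change of protocol wording, one CRF entry and one descriptive table. There are no extra patients or visits, and the primary analysis is unchanged.

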**Subject criteria**

A) The AD subjects

a) Inclusion criteria:

-Hospitalized patients diagnosed with untreated alcohol use disorder (confirmed by the diagnostic criteria of DSM-5).

-Male, age 18 to 55 years old, Han nationality, junior high school education or above,

right-handed.

-Those with normal eyesight, including corrected vision(screened clinically).

b) Exclusion criteria:

-The patient suffer from other mental illnesses (screen by DSM-V criteria).

-The patient has allergy reaction to medications use for conventional treatment of alcohol use disorder.

-The patient had a history of organic brain disease, a pacemaker, gastrointestinal surgery, or serious health problems.

-The patient had a history of seizures.

-The patient is complicated with severe physical disease.

-Patient has other drug dependence (except for nicotine dependence).

-The patient took drugs affecting intestinal flora 30 days before and during admission.

-The patient has participated in any other alcohol-related studies or trials within the past

30 days.

-Patients had use any prescription or over-the-counter drugs in the past 30 days that may

affect mood or alcohol cravings.

B）Healthy control group

a) Inclusion criteria:

-Male, age 18 to 55 years old, Han nationality, junior high school education or above,

right-handed.

-No history of psychoactive substance abuse, except tobacco (screen with urine dipstick test).

-Those with normal eyesight, including corrected vision (screen clinically).

-No alcoholic beverages in the last 2 weeks.

-According to the WHO healthy alcohol consumption standard, the average intake of

pure alcohol per week is less than 210 grams, or do not drink at all (screen clinically).

b) Exclusion criteria:

-Those who suffer from other mental illnesses (screen by DSM-V criteria).

-Those who has history of organic brain disease, a pacemaker, gastrointestinal surgery, or serious health problems.

-Those who has history of seizures.

-Those complicated with severe physical disease.

-Those with drug dependence, including alcohol dependence (exception for nicotine dependence).

-Those who took drugs affecting intestinal flora 30 days before and during admission.

-Those who has participated in any other alcohol-related studies or trials within the past

30 days.

-Those who use any prescription or over-the-counter drugs in the past 30 days that may

affect mood or alcohol cravings.

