**Data collection and research tools**

In this study, patients with alcohol dependence were given oral probiotics on the basis of conventional treatment. Stool samples and blood samples were collected before and after medication, and the changes of intestinal flora and blood biochemical indexes were analyzed and compared. The EEG changes before and after medication were detected by ERP, and the patients were evaluated regularly with Hamilton Anxiety Scale, Hamilton Depression Scale, alcohol withdrawal Symptom Scale, Pennsylvania Alcohol Desire Scale, etc. To investigate the therapeutic effect of probiotics on patients with alcohol dependence, the changes of intestinal flora and EEG in patients with alcohol dependence. Regular follow-up was performed outside the hospital. The recurrence rate after treatment was analyzed to determine the long-term efficacy of the treatment plan and provide reference and basis for clinical treatment.

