**Study flowchart**

**Figure 3.1. Flow chart of the study**

**Data analysis**

All data analysis will be performed using SPSS software version 25.0 (SPSS Inc, Chicago, IL, USA). Descriptive statistics for socio-demographic and clinical characteristics, CIWA-Ar, PACS, AUDIT, VAS, HAMD, and HAMA scores, ERP analysis, and serum pro-inflammatory cytokine levels will be computed. All categorical variables will be presented in frequency and percentage, while all continuous variables will be reported in mean and standard deviation or median and interquartile range, depends on normality. Differences in socio-demographic and clinical characteristics between the three groups will be computed with Pearson’s chi square test or one way ANOVA or Kruskal Wallis test.

The mean difference in the primary outcome (CIWA-Ar, PACS, AUDIT, and VAS scores) for the three randomized groups (ACT, probiotic, and palcebo groups) at each specific time point (pre-intervention, 2 weeks at completion of conventional treatment [t0], post-treatment at 8 weeks [t1], post-treatment at 12 weeks [t2], and post-treatment at 24 weeks [t3]) will be assessed using one way analysis of variance (ANOVA) followed by false discovery rate adjustment. For the main pool analysis, mixed ANOVA is used to determine the interaction between the groups (ACT, probiotic, and placebo groups) and time points (t0, t1, t2, and t3) on the primary outcome ( CIWA-Ar, PACS, AUDIT, and VAS scores; interaction = intervention × time; where time is a within-subject variable and intervention effect is a between-subject variable). The main effects of intervention in the groups and time points will be presented as estimated marginal mean and standard error of mean. The study’s primary analysis will follow the intention-to-treat (ITT) principle. The data analysis for the study’s secondary outcomes (severity of anxiety and depressive symptoms, pro-inflammatory cytokines, EEG characteristics, and fecal microbiota) will be conducted similarly to the primary outcomes’ calculation. Statistical significance will be two-tailed and set to p < 0.05.

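### The only stated route for learning of adverse events is the subject's own phone call, and scheduled contact in weeks 1–8 differs between ACT and the powder arms

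*Protocol*

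**What the plan says.** - **How events reach the team.** Under Ethical considerations (subject vulnerability), subjects hold a card with the team's contact details and "they are encouraged to maintain close contact by phone, to report any AE occurring in subjects". The CRF entry and the reporting flow chart (Figure 8) come into play once an event has become known. The instruments under Questionnaires include no adverse-event enquiry, and no section has anyone ask about events at an assessment or a therapy session.
- **ACT contact.** Test drug and treatment plan: "Enrolled AD patients will be treated under the ACT protocol for eight weeks", with sessions described as "Once a week, each treatment lasted about 1 hour".
- **Powder contact.** Same section: "Frequency of probiotics and placebo treatment: once a day, each time 2g, 8 weeks". No treatment visit is stated for either powder.
- **Shared contact.** Data analysis places assessments before the intervention and at weeks 2, 8, 12 and 24 in all three arms. All subjects enter as "Hospitalized patients diagnosed with untreated alcohol use disorder"; the length of stay is not given. Data collection and research tools adds "Regular follow-up was performed outside the hospital", without an interval or any adverse-event content.
- **End of intervention.** The treatment plan gives 8 weeks. The primary and secondary objectives describe week 24 as 12 weeks after the intervention ended.

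**The concern.** Unprompted reporting finds the events that a subject thinks worth a phone call. Milder events, and events that the subject does not connect with the study, tend to be lost. The protocol presents probiotics as safe, so a low recorded event count would be read as support for that, although it could equally reflect that nobody asked.

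The second issue is unequal opportunity. A weekly hour with a therapist is an occasion on which an event may be mentioned and passed on, and the powder arms have no counterpart. If that happens, ACT would show more events than the powders even with equal true rates, and its count could drop when the sessions stop. What is at stake is the safety reporting that Figure 8 feeds into the trial database and the clinical study report. The primary efficacy analysis is not affected.

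**Working it through.** The protocol states no adverse-event rate, so there is no figure to reproduce. The check is a count of scheduled contacts, followed by an illustration with declared assumptions.

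**Step 1: scheduled contacts after baseline** (Test drug and treatment plan; Data analysis)

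| | ACT | Probiotic | Placebo |
| --- | --- | --- | --- |
| Weeks 1–8, sessions | 8 | 0 | 0 |
| Weeks 1–8, assessments (weeks 2, 8) | 2 | 2 | 2 |
| **Weeks 1–8, total** | **10** | **2** | **2** |
| Weeks 9–24, assessments (weeks 12, 24) | 2 | 2 | 2 |

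Counted as distinct weeks with a contact, weeks 1–8 give 8 for ACT and 2 for each powder arm.

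**Step 2: dependence on the end of intervention.** The objectives imply 24 − 12 = week 12; the treatment plan says week 8. If weekly sessions ran to week 12, the count to that point would be 12 + 3 = 15 for ACT against 3 for each powder arm. The imbalance is present on either reading.

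**Step 3: ACT versus powder.** Let p be the true 8-week risk, equal in all arms; c the share of events captured by routes common to all arms (phone, or being noticed on the ward); and s the share of the remainder that comes to light at ACT sessions. None of the three is in the protocol.

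- Recorded risk on ACT = p[1 − (1 − c)(1 − s)]
- Recorded risk on either powder = pc
- False gap = p(1 − c)s

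With p = 0.20, c = 0.5, s = 0.5: ACT 0.20 × (1 − 0.25) = 0.15, or 5.4 of 36; powder 0.20 × 0.5 = 0.10, or 3.6 of 36. The gap is 5 points.

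Over c from 0.3 to 0.9 and s from 0 to 1:

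- p = 0.10: gap 0 to 0.10 × 0.7 × 1 = 7 points
- p = 0.20: gap 0 to 14 points
- p = 0.40: gap 0 to 28 points

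The gap is exactly 0 when s = 0, that is, if nothing said at a session reaches the CRF.

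**Step 4: probiotic versus placebo.** Scheduled contact is the same, so with a common c equal true risks give a false gap of 0. Unequal true risks p1 and p0 are recorded as c(p1 − p0). An assumed true 20% against 10% is recorded as 10% against 5% at c = 0.5; the 10-point difference shrinks to between 3 points (c = 0.3) and 9 points (c = 0.9). The share of powder events missed is 1 − c, here 10% to 70%.

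**Step 5: change over time.** Of the adverse-event routes, only the ACT sessions are scheduled to stop when the intervention ends. Setting s to 0 takes ACT from 15% to 10% in the example of step 3, for periods of equal true risk. With s = 0 throughout there is no drop. In the powder arms the phone route is unchanged and the visits only become sparser.

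**The case against.** The strongest reply is that no affected analysis exists. Adverse events appear in neither the primary nor the secondary objectives, nor in Data analysis or the shell tables, and no between-arm comparison of them is proposed. The phone route is the same in every arm, and nothing says that therapists ask about or record events. All arms begin on the ward, where staff may notice events whatever the arm. This stands in so far as it limits the point to safety reporting and leaves the size of any bias unknown. It does not answer the lack of a scheduled enquiry: how events are elicited is a rule of conduct, and the protocol has set it as a phone call by the subject.

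Three stronger readings are tempting, and the documents do not support them:

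- *Recorded rates must differ by arm.* They may differ. If sessions contribute no reports, the gap is zero.
- *The probiotic is the least observed arm.* Probiotic and placebo share a regimen, assessments and follow-up, so they tie, and the contrast that isolates the powder's harms has equal scheduled contact.
- *Events must fall after week 8.* A drop is possible only through the end of ACT sessions. The time at which ward observation ends is not stated, and the end of the intervention is itself given in two ways.

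A fair objection to the remedy also stands in part. The sampling section says that subjects are not blinded and that data collectors do not know the objectives. An open question may lead a subject to mention therapy sessions to the person scoring the scales.

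**Conclusion.** The point holds in a limited form. Adverse-event capture rests on unprompted calls with no scheduled enquiry, so events can be missed in all arms. Scheduled contact in weeks 1–8 is 10 on ACT against 2 in each powder arm. An ACT-versus-powder tabulation would therefore be open to a bias of unknown size, possibly zero; under the model any such bias would inflate the ACT count. Probiotic versus placebo is affected by under-capture, which hides events and shrinks a real difference, and not by unequal contact.

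The contact counts follow from the protocol. The percentages do not: they rest on assumed values of p, c and s and show only how far the answer depends on them, so no single ratio should be quoted. The probiotic–placebo conclusion also assumes that subjects in the two powder arms are equally ready to phone, which fits powders described as alike in colour and taste. The efficacy analysis is untouched. The change is worthwhile because it is cheap and removes the imbalance in enquiry whatever its true effect.

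**What to change.** In the adverse-event text under Ethical considerations:

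1. At each existing assessment (weeks 2, 8, 12 and 24), ask every subject in all three arms the same open question about adverse events since the last visit. Ask it after the outcome scales are completed, so that disclosure of the arm cannot influence them at that visit.
2. Add a source field to the CRF (asked at visit, phoned in, seen on the ward, mentioned at an ACT session), allowing more than one source per event, so that an event phoned in and later reported at a visit counts in both.
3. Base any between-arm safety summary on events elicited at the common visits. List those known only from other sources separately. Keep the phone route and the reporting flow as they are.
4. Reconcile the objectives with the treatment plan on when the intervention ends.

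The cost is one question at visits that already take place and one CRF field. More minor events will be recorded, and some risk remains that the assessor learns the arm and carries that knowledge to later visits. Recall over the gaps of 6 weeks (week 2 to 8) and 12 weeks (week 12 to 24) will be incomplete, but the enquiry and the recall window will be the same in every arm.
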